**Table 2 Tab2:**
[figure not shown]
Schedule of enrolment, interviews, intervention, and assessment of the Housewives Ergonomic Intervention (HEI) trial, following the Standard Protocol Items Recommended for Clinical Trials (SPIRIT) guidelines

### Phase 1: The qualitative exploration

The qualitative study will be completed over 6 months. Semi-structured interviews with open-ended questions, and conventional qualitative content analysis methods will be conducted to investigate the biomechanical and psychosocial risk factors affecting WMSDs among the participants [27]. The interviews will take place face-to-face in a mutually convenient quiet environment without the presence of others. An interview guide has been prepared in line with the aim and objectives of the study. The initial question is a very general open-ended question around the participant’s work in the house, and they will be requested to provide a detailed answer [25]. Then further probing questions are asked according to this answer. The goal is to achieve a full understanding of the ergonomic and psychosocial circumstances of each participant’s WMSDs.

After completing each interview, it will be transcribed in full. The transcript will be then sent to each participant with a summary of key topics in each interview to ensure that the researcher has accurately interpreted the participants’ statements (member checking) [26], and if there are any ambiguities and inconsistencies, they will be resolved.

In addition, in parallel, we will use the Job Safety Analysis (JSA) by observation [28] to identify the most common musculoskeletal risk factors and harmful behaviors affecting the musculoskeletal health of each of the women in the study, to get an insight into their inability to protect their musculoskeletal health in their daily life. Finally, using the two approaches mentioned above (interview and observation), a health promotion model that best fits the qualitative study results will be developed.

### Phase 2: The randomized controlled trial

Randomized controlled trials (RCTs) represent the most powerful way to evaluate public health interventions. Randomized controlled trials minimize the impact of confounding bias as the assignment of each of the study participants to an intervention group or the control group will be done solely by chance [29]. The flow chart of the randomized controlled protocol is shown in Fig. 1.

**Fig. 1 Fig1:**
[figure not shown]
The flow chart of the randomized controlled protocol

### The intervention programs

The conceptual framework of the health promotion model will be developed based on phase 1 findings from the qualitative study. Recruitment of women who meet the inclusion criteria will continue until the required sample size is achieved. At this point, all participants will be coded and blindly allocated into one of four intervention groups by the researchers using a permuted block randomization program: (1) biomechanical, (2) psychosocial, (3) multidisciplinary (biomechanical and psychosocial), or (4) control. Based on the design of the randomized controlled trial intervention, the impact of the different intervention programs on musculoskeletal disorders, work ability, and quality of life of the housewives will be evaluated. As shown in Fig. 1, measures will be collected at baseline, after 3 months, and after 6 months of following their respective program.

To implement the content of the three intervention programs, a participatory ergonomic approach will be used. The effectiveness of this approach in ergonomic interventions depends on the ability and active cooperation of participants [29]. The required training content for participants in the psychosocial intervention will be provided following the conceptual framework developed in the qualitative study and the resulting theory. Similarly, for participants in the biomechanical intervention group, the required training will be provided following the conceptual framework derived from the qualitative study and job safety analysis (JSA) method. Finally, the multidisciplinary intervention group will receive the training provided to the psychosocial and biomechanical groups: that is, they will do both interventions. The multidisciplinary groups will receive both of the other two interventions in full.

After providing the required training programs, the 40 participants in each of the three intervention groups will be divided into 4 subgroups of ten participants. There will be an expert, as a facilitator, who will each manage one of the 12 subgroups, overseen by a coordinator. Subgroup meetings will be held weekly to retrain the materials taught to the group members and discuss the actions taken by the members of the subgroups. The facilitators will be responsible for reviewing the training content provided to the participants in their subgroup, discussing the experiences of and the actions taken by the members of their subgroups, and performing the required assessment during the intervention period. The facilitators of the intervention groups will communicate with each other by forming a social group through virtual networks and face-to-face meetings and share the experiences of their subgroups with each other. The facilitator coordinator will ensure all aspects of the subgroup training and associated interactions are appropriate and intervene if necessary, to reduce any foreseeable risk of harm. The study group evaluators will remain blind to group allocation throughout the intervention, including knowledge of withdrawal from the study.

The facilitators will be provided with training for their role that will include information on how to manage work teams and how to use the risk assessment methods and other tools used in the present study. It will be made clear that the facilitators should not interfere in the participant’s training procedures or in the implementation of the interventions; their purpose is to play a facilitating role based on the principles of participatory ergonomics. In order to ensure the implementation of the interventions, reminder messages will sent to the participants on a weekly basis through virtual network. After the final evaluation and comparisons of the three intervention groups, the participants in the control group also will receive the most effective intervention, in accordance with ethical principles.

The program logic model developed based on the participatory ergonomic approach is presented in Fig. 2. The model provides an explanation of the study phases, the conceptual framework of participatory ergonomic approach and how it is implemented, the health promotion training program, and the process used to assess the expected outputs.

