**Inclusion criteria**	
Working-aged woman aged 20–65 years	
Diagnosed MSD and an MSD pain intensity score of 4 and higher based on the visual analog scale (VAS) [25, 26].	
The motivation and willingness to fully participate with any randomly allocated intervention	
Being married and living with the family	
Having no job other than housekeeping	
Not pregnant, nor breastfeeding	

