### Instruments

The instruments that will be used to collect the data are the Rapid Entire Body Assessment (REBA) [32], the Visual Analog Scale (VAS) [33], the Work Ability Score (WAS) [34], the Hospital Anxiety and Depression Scale (HADS) [35], and the 36-item Short-Form Health Survey (SF-36) [36]. Table 3 presents the general features of the mentioned instruments.

**Table 3 Tab3:** Summary of the instruments used for data collection

Scale	Content	Scoring
VAS	Pain intensity	0 (no pain)–10 (severe pain)
REBA	The Rapid Entire Body Assessment	1 (no need for assessment), 11––15 (immediate assessment is required)
WAS	Work ability	0 (inability to perform activities)–10 (ability to perform activities)
HADS	The Hospital Anxiety and Depression Scale	0 (lowest anxiety/depression level)–21 (highest anxiety/depression level)
SF-36	Health-related quality of life	7 subscales: 0 (the worst)–100 (the best)

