### Sample size and power calculations

Following the study conducted by Shariat [37], which similarly used a three-arm, parallel, RCT to investigate MSDs in office workers, the sample size we require in the quantitative phase to provide ample power was calculated as 30 persons for each group. This sample size was calculated to be sufficient at an alpha of 0.05 and a power of .80, to test for a difference between the groups. Nevertheless, sample size calculations are sensitive to error and complicated when drawing upon incomplete information in the literature [38]. Additionally, experience indicated we must consider a potential dropout rate of 30%. Hence, according to the following formula, we should work with an initial recruitment target of 40 participants in each group:
$$ n=\frac{{\left({Z}_{1-\frac{\alpha }{2}}+{Z}_{1-\beta}\right)}^2\left({\delta_1}^2+{\delta_2}^2\right)}{{\left(\overline{{\overline{X}}_1}-{\overline{X}}_2\right)}^2}=\frac{{\left(1.96+0.84\right)}^2\left({20.2}^2+{21.1}^2\right)}{{\left(-15\right)}^2}=29.9\cong 30 $$

N=30+30(0.3)≅40

In line with this approach, a total of 160 housewives aged 20–65 years with WMSDs will be recruited based on the health records available in the health centers of Akbarabad-Kavar city by taking into account the inclusion and exclusion criteria given in Table 1. Participants will be allocated into four groups (the three intervention groups plus one control group) based on permuted block randomization. The allocation is concealed by using opaque, sealed envelopes that are consecutively numbered and included each group’s name. Sampling using this randomization process gives each participant an equal chance of being placed in each group [39].

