### Data analysis

#### Phase 1

To perform the process of qualitative content analysis, the audio file of each interview will be listened to attentively several times on the same day and it will be transcribed verbatim. To keep the data from the interviews confidential, a code will be assigned to each transcript. To come up with a general impression of the interviews and become fully immersed in the data, the audio files of the interviews and the transcripts will be reviewed several times, and any possible ambiguities and inconsistencies will be removed by comparing the audio files and the transcripts. The interviews will be audiotaped and a summary of the key issues in each interview will be then sent to each participant to ensure that the researcher will have accurately interpreted that participant’s comments (a “member check”) [26]. The process of data analysis will be performed continuously and simultaneously with the data collection process. All words, sentences, and paragraphs that are related in the analysis process will be considered as a single semantic unit. After merging the semantic units, the codes will be extracted. The codes together form the subcategories and then the main categories. Finally, upon the abstraction of the categories, the relevant themes will be identified. MAX.QDA software will be used to manage the data [40].

#### Phase 2

The collected data will be analyzed with SPSS software using descriptive statistics (including frequency, frequency percentage, mean, and standard deviation) and inferential statistics. We will undertake both “intention to treat” and “per protocol” approaches to the inferential statistical analyses to achieve fully understand the outcomes and manage bias in the face of any drop out. To compare the differences between the values obtained before the intervention and 3 and 6 months after the intervention in each group, generalized mixed models of analysis of variance for repeated measures will be used. We will also calculate differences between means of the independent groups with their respective 95% confidence intervals. All tests will be performed at a significance level of 0.05 (p <0.05). The Kolmogorov-Smirnov test will be used to test the normality of the data. The per protocol analyses will only include the participants who complete the intervention to which they were allocated.

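### Allocating all 160 women together, with a screening pain score on file, is valid, but no baseline factor is named and no baseline adjustment is stated, so available precision is left unused

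*Protocol article*

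**What the plan says.** Under The intervention programs, the protocol article fixes the timing: "Recruitment of women who meet the inclusion criteria will continue until the required sample size is achieved. At this point, all participants will be coded". The allocation itself reads: "all participants will be coded and blindly allocated into one of four intervention groups by the researchers using a permuted block randomization program". Sample size and power calculations repeats the method ("Participants will be allocated into four groups (the three intervention groups plus one control group) based on permuted block randomization") and adds the concealment device: "The allocation is concealed by using opaque, sealed envelopes that are consecutively numbered". Neither section names a stratification factor or any other use of a baseline value.

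Table 1 requires for entry "Diagnosed MSD and an MSD pain intensity score of 4 and higher based on the visual analog scale (VAS"), so a pain score exists for each woman before allocation. VAS is also one of five outcome instruments; Table 3 scores it "0 (no pain)–10 (severe pain").

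Data analysis, Phase 2, plans repeated-measures mixed models on baseline, 3 and 6 months, worded as comparisons within each group. On the between-group side it says: "We will also calculate differences between means of the independent groups with their respective 95% confidence intervals". It mentions no baseline covariate.

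**The concern.** Permuted blocks over an entry sequence keep arm sizes even as recruitment proceeds. When the whole list exists before a single allocation, blocks over code order secure 40 per arm and little else. Batch allocation offers the chance to balance on a known score, and the plan as described does not take it.

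The research question makes this relevant. The protocol asks which of three interventions is most effective, and the control group is later to receive that one. A ranking of similar active arms is more easily swayed by a chance head start than one contrast with control. If the between-arm comparison does not adjust for baseline, part of any head start carries into the estimate, and the interval is wider than it needs to be.

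**Working it through.** **The plan's own figure.** Inputs from Sample size and power calculations: SDs 20.2 and 21.1, difference 15, 1.96 and 0.84.
n = (1.96 + 0.84)² × (20.2² + 21.1²) / 15² = 29.73, printed as 29.9 and rounded to 30. The target per group reproduces. Recruitment is 40 per arm; the stated 30% dropout leaves 40 × 0.7 = 28.

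**Chance imbalance, 40 per arm, no baseline factor.** The SE of a two-arm difference in baseline means is √(2/40) = 0.224 SD, a 95% range of ±1.96 × 0.224 = ±0.44 SD. For the largest gap among four arms (simulated, normal baselines):

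| Largest gap exceeds | Probability |
|---|---|
| 0.25 SD | 0.68 |
| 0.40 SD | 0.28 |
| 0.50 SD | 0.11 |

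The median largest gap is 0.31 SD.

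**What a gap does.** Let g be the baseline gap and r the baseline to follow-up correlation. The document gives no r, so 0.3 to 0.7 is assumed. A comparison of follow-up means shifts by r × g. A comparison of changes from baseline shifts by −(1 − r) × g. With g = 0.4 SD and r = 0.5, either shifts by 0.2 SD in size. Including baseline as a time point in an unconstrained repeated-measures model therefore does not by itself remove the effect. A baseline covariate or a common-baseline constraint does.

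**What adjustment gains.** The variance of an adjusted follow-up difference is (1 − r²) times that of the unadjusted one. Power is at the plan's standardised difference, 15/20.65 = 0.73, two-sided 5%, one pairwise comparison, where 20.65 is the root mean square of the two SDs.

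| r | Variance factor | SE, 40 per arm (SD) | Power, 40 per arm | Power, 28 per arm |
|---|---|---|---|---|
| unadjusted | 1 | 0.224 | 0.90 | 0.78 |
| 0.3 | 0.91 | 0.213 | 0.93 | 0.81 |
| 0.5 | 0.75 | 0.194 | 0.96 | 0.88 |
| 0.7 | 0.51 | 0.160 | 0.995 | 0.97 |

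**What stratified allocation gains.** If the stratifying score were the baseline score itself, a median split would cut the SE of the baseline difference from 0.224 to about 0.135 SD, and quartile strata to about 0.084 SD. At r = 0.5 the SE of an unadjusted follow-up difference would fall from 0.223 to 0.205 or 0.198 SD (simulated). Adjustment alone already gives 0.194, so stratification adds little precision on top of it; its further benefit is visible balance.

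**How far the screening score serves.** Recruitment was planned from November 2020 to April 2021 (Trial status), so an early entrant's screening score could be about five months old at allocation. In rank-ordered blocks of four, with an assumed screening to baseline correlation of 0.7, the chance of a baseline gap above 0.4 SD is about 6%. At 0.5 it is about 16 to 17%, against 28% with no baseline factor.

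**The case against.** The strongest reply is that nothing here is an error. Unstratified permuted blocks are valid, and chance imbalance is already reflected in the standard error, the confidence interval and the 5% error rate. That stands: there is no bias and no stated figure is wrong. What remains is a better use of data the trial collects anyway.

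A second reply is that a condensed article may leave stratification factors and covariates to a fuller document. That partly stands. The article does not say that no factor is used; it names none, in two separate descriptions of the randomisation.

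Several stronger readings are tempting and are not supported:

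- **The arms will be compared as raw means.** The text does not say raw or unadjusted. The means could be model-based or change scores, and mixed models including baseline are planned beside them. The text supports only that no baseline adjustment is stated.
- **Sorting by VAS would abolish imbalance.** That holds only if screening VAS equals baseline VAS, which the document does not say.
- **Every outcome could be balanced free of charge.** Only VAS is shown to be known before allocation. The timing of REBA, WAS, HADS and SF-36 relative to allocation is not readable, since Table 2 and Fig. 1 are not shown. Ordering on VAS balances them only as far as they correlate with it.
- **A VAS gap can be set against the planned 15-point difference.** That difference belongs to an unnamed outcome and cannot lie on the 0 to 10 VAS in Table 3.
- **There is certainly no entry sequence.** Consecutively numbered envelopes are a usual device for one-by-one allocation, so the two descriptions leave the mechanics unclear.

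**Conclusion.** The point holds as an optional improvement. Allocation is described as one batch after recruitment, with a screening VAS on file, no baseline factor named and no baseline adjustment stated for the between-group differences. A largest gap above 0.4 SD is expected in about 28% of allocations. If the comparison is not adjusted, the variance given up is about 9%, 25% or 49% at r = 0.3, 0.5 or 0.7. The gain matters most if dropout reaches the stated 30%: at the plan's own effect size, power with 28 per arm is 0.78 unadjusted and 0.88 adjusted at r = 0.5.

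This rests on assumed correlations and on normal baselines. Restricting entry to VAS of 4 or more may lower r for pain, and with it the gain. If an analysis plan not shown already adjusts for baseline, the precision loss disappears and only the balance of the allocation is left to discuss.

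**What to change.** 1. State in Data analysis that between-arm differences at 3 and 6 months, for every outcome, come from a model that adjusts for the baseline value of that outcome or constrains a common baseline mean across arms. This brings most of the precision gain, uses baseline measurements already planned, and remains available whether or not allocation has taken place. Cost: one sentence.
2. If allocation has not yet taken place, stratify the coded list by screening VAS, or order it by that score, before running the same permuted-block program. Include that factor in the model. Say plainly that this balances pain only, and only as far as the screening score tracks the baseline score. Cost: sorting an existing list and one sentence in the randomisation paragraph; no new data or visits.
3. Reconcile the batch allocation under The intervention programs with the consecutively numbered envelopes under Sample size and power calculations, stating whether women are allocated together or one by one and how the envelopes are used.

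### The three intervention arms are delivered in facilitator-led subgroups of ten, but the sample size assumes independent women and the named model has no subgroup level

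*Protocol article*

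**What the plan says.** Protocol article, The intervention programs: after the training has been given, "the 40 participants in each of the three intervention groups will be divided into 4 subgroups of ten participants". Facilitators are experts "who will each manage one of the 12 subgroups, overseen by a coordinator". The subgroups meet weekly to go over the material again and to discuss what members have done. No subgroups are described for control.

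Sample size and power calculations: "Participants will be allocated into four groups (the three intervention groups plus one control group) based on permuted block randomization", so the unit of randomisation is the woman. The required number is "calculated as 30 persons for each group", described as "sufficient at an alpha of 0.05 and a power of .80, to test for a difference between the groups". The formula is the usual one for two independent means. Its only inflation is for loss to follow-up ("we must consider a potential dropout rate of 30" per cent), which takes the target to 40 per group and 160 in all.

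Data analysis, Phase 2: "generalized mixed models of analysis of variance for repeated measures will be used", together with mean differences between groups and 95% confidence intervals. Neither section mentions subgroup, facilitator, an ICC or a design effect.

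**The concern.** This is an individually randomised but partially nested trial: women in three arms share a facilitator and a weekly discussion group, and women in the fourth do not. Shared discussion is part of the participatory programme, so some within-subgroup correlation is plausible. A repeated-measures model deals with correlation between visits of the same woman. It does not deal with correlation between women in the same subgroup.

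If that correlation is positive, the variance of an intervention-arm mean is larger than the independence formula says. The penalty is full when two intervention arms are compared and halved against control, where only one arm is clustered. The Background hypothesises that the combined programme beats each single programme, and that is the contrast with the full penalty. Each arm's result would also rest on four subgroups whose facilitators, as described, serve no other arm, so differences between facilitators could add to an apparent difference between programmes. After the comparisons, control women are to be offered the programme found most effective, so the ranking has a practical consequence.

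**Working it through.** **Inputs from the protocol article.** Two-sided alpha 0.05 and power 0.80 (z = 1.96 and 0.84); SDs 20.2 and 21.1; difference 15; 40 recruited per arm; 30% dropout; 4 subgroups of 10 in each intervention arm.

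**Assumed.** ICC 0.01 to 0.10, because the documents give none.

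**The plan's own figure.** n = (1.96 + 0.84)² × (20.2² + 21.1²) / 15² = 7.84 × 853.25 / 225 = 29.7, so 30 per group is reproduced (the printed 29.9 is a trivial difference). Power at 30 per group is 0.803, with all women independent.

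**Effect of dropout alone.** 40 × 0.7 = 28 analysed per arm. The common variance is 853.25 / 2 = 426.6 (SD 20.65). SE = √(2 × 426.6 / 28) = 5.52, and power = Φ(15/5.52 − 1.96) = 0.776. This is the zero-ICC baseline for the first scenario below.

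**Clustering.** With m women per subgroup, DE = 1 + (m − 1) × ICC. The variance multiplier V is DE between two intervention arms and (DE + 1)/2 against control.

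- Power of a test that uses the correct SE = Φ(15 / (SE × √V) − 1.96), where SE is the independence value.
- True type I error of a nominal 5% test that ignores subgroups = 2 × [1 − Φ(1.96/√V)].

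Example: m = 7 and ICC 0.05 give DE = 1 + 6 × 0.05 = 1.30. Between intervention arms V = 1.30; against control V = 1.15.

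The first figure in each pair is between two intervention arms, the second is against control (normal approximation).

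| Scenario | ICC | DE | Power | Type I error if ignored |
|---|---|---|---|---|
| 28 per arm, m = 7 (30% loss) | 0 | 1.00 | 0.776 / 0.776 | 5.0% / 5.0% |
| | 0.01 | 1.06 | 0.752 / 0.763 | 5.7% / 5.3% |
| | 0.05 | 1.30 | 0.664 / 0.717 | 8.6% / 6.8% |
| | 0.10 | 1.60 | 0.575 / 0.664 | 12.1% / 8.6% |
| 40 per arm, m = 10 (no loss) | 0 | 1.00 | 0.901 / 0.901 | 5.0% / 5.0% |
| | 0.01 | 1.09 | 0.875 / 0.888 | 6.0% / 5.5% |
| | 0.05 | 1.45 | 0.769 / 0.835 | 10.4% / 7.7% |
| | 0.10 | 1.90 | 0.654 / 0.769 | 15.5% / 10.4% |

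The last two columns describe different analyses: the power applies if clustering is allowed for, the type I error if it is not.

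**Few subgroups.** The normal approximation is generous with 4 subgroups per arm. With t references (6 degrees of freedom between intervention arms, Satterthwaite against control), power at 28 per arm and ICC 0.05 is about 0.52 and 0.62.

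**The case against.** The analysis half rests partly on silence. A reader might infer that the model is confined to repeated measures; the article does not say so. A mixed model can carry a subgroup effect, and the random-effects structure is often left to a statistical analysis plan, which is not at hand. That stands. Such a plan could repair the intervals, but it could not make the sample size calculation allow for clustering.

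A reader might also take within-subgroup correlation, and so intervals that are too narrow, as certain. The documents do not support that. They give no ICC, and The intervention programs section describes features that may keep it low: training comes before the split into subgroups, facilitators are told not to interfere in training or implementation, they share experience across subgroups, and a coordinator oversees them. This makes the low end of the range credible, although weekly group discussion remains.

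Two readings of the figures would overstate the case. One sets the type I error under full retention (up to 15.5%) beside the power after 30% loss (down to 0.575); these belong to different scenarios. The other compares 0.664 with the planned 0.80 and blames clustering for the whole gap, when 0.776 is already the figure with no clustering. The Discussion also expects low attrition, and with full retention power against control is still 0.835 at ICC 0.05.

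**Conclusion.** The point holds in conditional form. The sample size calculation makes no allowance for clustering, and the analysis as described names no subgroup level, although the article itself fixes subgroup delivery in three of the four arms. For any positive ICC the resulting intervals are too narrow for contrasts involving an intervention arm.

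The size depends on an ICC that has to be assumed. After the planned 30% loss, clustering costs 1 to 2 points of power at ICC 0.01. At ICC 0.05 it costs 11 points between intervention arms (0.776 to 0.664) and 6 against control (0.776 to 0.717); at 0.10 it costs 20 and 11. Small at the bottom of the range, it is material from about 0.05, and always larger for multidisciplinary versus single programmes than for comparisons with control. The documents do not establish where in that range this trial lies.

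**What to change.** 1. Record the subgroup (and hence facilitator) of every woman in the three intervention arms. Membership may be hard to recover later.
2. In Data analysis, Phase 2, add a random subgroup effect to the mixed model in the three intervention arms only, with control women as singletons, and use Satterthwaite or Kenward-Roger degrees of freedom.
3. In Sample size and power calculations, state that the 80% power assumes zero ICC. Give power over ICC 0.01 to 0.10 for both types of contrast, under one stated retention assumption at a time and with the zero-ICC figure beside it.

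The cost is one data field, one model term and a short addition to the text; recruitment and delivery do not change. The drawback is wider intervals and a subgroup variance estimated from only 4 subgroups per arm, so it will be imprecise and the degrees of freedom few. The change makes the stated uncertainty honest, but it does not restore the planned power.
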